### Participants

#### Sample size

Sample size consideration is mostly based upon fatigue as the primary outcome measure; this is the outcome measure used most frequently in other trials that include people with fatigue. As a variety of fatigue measures have been used in other trials, we have used standardised effect sizes to enable comparisons between them. Standardised effect sizes of 0.2 are commonly considered small, 0.5 considered medium, and 0.8 considered large [47]. In this trial, we will aim to detect a medium effect size. The Cochrane systematic review of cognitive behavioural therapy in people with CFS [38] identified two good quality studies, and in these the standardised effect sizes for fatigue were 0.7 and 1.0. The Cochrane Systematic Review of Amantadine for fatigue in MS found effect sizes of between 0.3 and 1.4 for the three studies that measured fatigue on a continuous scale [21]. Thus, our choice of an effect size seems reasonable in the context of (a) how well cognitive behavioural approaches work in another chronic disease where fatigue is a major symptom, and (b) how well another treatment for fatigue works in MS. For 85% power, the sample size requirement (using a two-tailed 5% significance level) is 73 people per arm of the trial; 146 in total. Inevitably, there will be some participants who withdraw from the trial during its course, or more generally, do not complete outcome measures. To allow for this, we will aim to enrol 180 participants; 90 in each arm of the trial. Thus, if 20% of participants do not provide data on the primary outcome measures, the study would maintain statistical power. This figure of 20% will be reviewed during the study and sample size adjusted up or down accordingly.

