#### Source of participants

The recruitment target for each of the three centres will be 60 people, of whom 30 will receive the group-based intervention. In each centre this will require running three successive iterations of the programme, recruiting in blocks of around 20. The fatigue management programme has been designed for groups of between 6-12 participants.

Participants will be recruited using a variety of methods; via MS Services/Neurology Departments, MS Society newsletters and website, other relevant newsletters, MS Research database, MS support groups, General Practitioners.

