## Results

### Statistical analysis

We will conduct two sets of statistical analyses. The primary analysis will be an intention-to-treat analysis, whereby participants are analysed in the arm of the trial they were randomised to, regardless of how many sessions of the programme they attend. In order for an intention-to-treat analysis to be conducted, we will endeavour to collect outcome measures for everyone (while recognising the right of participants to withdraw from the trial at any stage). The secondary analysis will be conducted on a "per protocol" basis. This analysis will exclude participants who attend fewer than four sessions of the fatigue management programme.

Data will be analysed primarily using SPSS for Windows. A 5% significance level will be used. Outcome measures will be assumed to be interval scaled, and the analysis will initially be focused on absolute change in outcome post-intervention relative to baseline, and absolute change in outcome at 4- and 12-month follow-up, relative to baseline. These change scores, presented separately for the three follow-up periods, are being used because we think they are the most clinically useful. They are likely to be normally distributed (this assumption will be checked). Change scores will be compared between the two groups using the independent samples *t*-test.

Additional analyses will be conducted to address the following issues:

1. We will adjust for baseline variability/baseline differences between treatment arms. For each outcome variable analysed, these would include the baseline measurement for that outcome, baseline primary outcome measures, gender, age, marital status, education level, type of MS, time since diagnosis, and level of disability.

2. Although participants in the trial have been randomised individually, for those randomised to the fatigue management intervention, it is possible that the group-based nature of the intervention will result in observations that are clustered. This could result in misleading statistical tests [74]. We will assess the extent to which this occurs by incorporating clustering into the analysis.

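### The main t-test and the sample size make no allowance for clustering in the roughly nine FMP groups, a risk the protocol itself names and leaves to an additional analysis

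*Protocol article*

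**What the plan says.** The Statistical analysis section of the Protocol article sets a 5% level and names the main comparison: "Change scores will be compared between the two groups using the independent samples" *t*-test, at each follow-up.

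The second item in its list of additional analyses takes up the group format. For the FMP arm "it is possible that the group-based nature of the intervention will result in observations that are clustered". The protocol adds that tests may mislead as a result, and that clustering will be built into an analysis to see how far this happens. The section later says that the additional analyses will include multi-level or mixed models.

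The Sample size section states: "For 85% power, the sample size requirement (using a two-tailed 5% significance level) is 73 people per arm of the trial; 146 in total". The target is given as "In this trial, we will aim to detect a medium effect size", with 0.5 defined as medium. Enrolment is raised to 180, and the only reason given is missing data: "if 20% of participants do not provide data on the primary outcome measures, the study would maintain statistical power". The planned review of the sample size concerns that 20% figure alone.

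On group structure, Source of participants says: "In each centre this will require running three successive iterations of the programme, recruiting in blocks of around 20". There are three centres, each with 30 people in the FMP arm. Under Randomisation, each block from a centre is split half to FMP and half to current local practice.

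**The concern.** FMP participants share sessions, two facilitators and a peer group whose contact outside sessions is encouraged. Controls share none of this. If outcomes within an FMP group become alike because of it, the FMP mean rests on fewer independent units than its head count. The t-test then uses too small a standard error, its p-values and intervals are too optimistic, and a valid test has less power than stated.

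The protocol recognises the mechanism but keeps the exposed test as the headline analysis for all three primary outcomes. Clustering also plays no part in the sample size.

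**Working it through.** **Inputs from the protocol.** Two-sided alpha 0.05; power 85%; standardised effect 0.5 (SD = 1); 73 per arm; 180 enrolled, 90 per arm; 20% loss; 3 centres x 3 iterations = 9 FMP groups; 90/9 = 10 randomised per group. After 20% loss, 72 per arm and 72/9 = 8 per group.

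**Assumed.** The FMP-group ICC (rho), because none is given. Range shown: 0 to 0.10.

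**Step 1: the plan's own figure.** The two-sample t-test formula gives 72.8, so 73 per arm, with power 85.1% at 73. The normal formula, 2 x (1.960 + 1.036)^2 / 0.5^2, gives 71.8. The stated figure reproduces as an individual-level calculation, that is, with a design effect of 1.

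**Step 2: the attrition sentence.** 180 x 0.8 = 144, below 146. Power at 72 per arm is 84.6%. The loss that 180 can absorb is 1 - 146/180 = 18.9%.

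**Step 3: clustering in the FMP arm only.** With n per arm and m per group:

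- True variance of the difference: [1 + (m - 1)rho]/n + 1/n. The t-test uses 2/n.
- Ratio of true SE to t-test SE: sqrt{[2 + (m - 1)rho]/2}.
- Type I error of the t-test: 2[1 - Phi(1.960/ratio)].
- Power of a valid test: Phi(0.5/SE - 1.960), or noncentral t with Satterthwaite df from 8 and n - 1 df.

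Example, rho = 0.05, m = 8, n = 72: the design effect is 1 + 7 x 0.05 = 1.35. The ratio is sqrt(2.35/2) = 1.084. Type I error is 2[1 - Phi(1.808)] = 7.1%. SE = sqrt(2.35/72) = 0.181, and power is 79.0% (normal) or 75.5% (22.8 df).

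| ICC | Design effect, FMP arm | SE ratio | t-test type I error | Power, normal | Power, small-sample df |
|---|---|---|---|---|---|
| 0 | 1.00 | 1.00 | 5.0% | 85.1% | 82.6% |
| 0.01 | 1.07 | 1.02 | 5.4% | 83.9% | 81.2% |
| 0.02 | 1.14 | 1.03 | 5.8% | 82.6% | 79.7% |
| 0.05 | 1.35 | 1.08 | 7.1% | 79.0% | 75.5% |
| 0.10 | 1.70 | 1.16 | 9.2% | 73.3% | 68.9% |

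A simulation of 40,000 trials per setting agrees: t-test type I error is 5.7%, 7.2% and 9.4% at ICC 0.02, 0.05 and 0.10. A Satterthwaite test on group means stays between 5.0% and 5.2% at these ICCs.

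**Step 4: no loss (90 per arm, groups of 10).** Power (normal / small-sample df) is 89.5% / 87.1% at ICC 0.02, 85.8% / 82.5% at 0.05, and 79.5% / 75.0% at 0.10. The t-test's type I error is then slightly higher than in the table: about 6.1%, 7.7% and 10.4%.

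**Step 5: correlation shared by both arms.** If the correlation comes from the centre-by-iteration block, it cancels in the difference. The true variance is 2(1 - rho)/n while the t-test still uses about 2/n. At rho = 0.05, 1.960/sqrt(0.95) = 2.011, a type I error of about 4.4%. Simulation gives 4.4% at 0.05 and 4.1% at 0.10. With the FMP ICC split evenly between shared and FMP-specific parts, simulated type I error is about 5.9% at a total of 0.05 and 6.5% at 0.10.

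**The case against.** A reader might infer three stronger things that the documents do not support.

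- **That clustering is ignored.** It is not. The protocol names it and pre-specifies an analysis that includes it. What remains at fault is the order of the analyses and the sample size.
- **That any within-group correlation makes the p-values too small.** Each block supplies controls from the same centre and iteration, so a shared component makes the t-test slightly conservative. Only FMP-specific correlation inflates the error, and how the ICC would split is unknown. The table is the case in which all of it is FMP-specific.
- **That the trial falls short of 85% power as a matter of fact.** The protocol says only that clustering is possible. At ICC zero the t-test is valid and has about 85% power. With little attrition, the margin up to 180 absorbs a small ICC. About 2 points of each small-sample figure come from the df method, not from clustering (82.6% against 84.6% at ICC zero).

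All this limits the size of the point. What stands is that the t-test is exposed to the one kind of correlation that the group format could create. Nine groups estimate an ICC poorly, so finding no clear clustering afterwards would not vindicate the t-test. Better retention helps power but does not protect the test's level.

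The attrition shortfall is fairly called minor: 84.6% against 85.1%. It is an arithmetic slip and adds no weight to the clustering point.

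**Conclusion.** The point holds conditionally. The main test and the figure of 73 per arm make no allowance for clustering in about nine FMP groups. If FMP-specific correlation is 0.02 to 0.10 and 72 per arm are analysed, the nominal 5% test runs at about 6-9%. Power for 0.5 SD is then about 73-83% (normal) or 69-80% (small-sample df), against the stated 85%. If all 180 give data, power at ICC 0.05 is 82.5-86%. If part of the correlation is shared between arms, the inflation is smaller or absent. These figures rest on an assumed ICC, equal group sizes and a total SD of 1 in both arms.

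Without any such assumption, the sentence that power is maintained at 20% loss is wrong by two participants.

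**What to change.** - Make the clustered analysis, which is already planned, the primary one for the three primary outcomes. Use a partially nested mixed model with a random treatment-group effect in the FMP arm only, a centre (or centre-by-iteration block) term to match the randomisation, arm-specific residual variances, and Satterthwaite or Kenward-Roger df. Keep the group effect in the model whatever its estimate.
- Keep the independent-samples t-test as a supportive analysis.
- Replace the flat 85% with power over an assumed range of ICC (for example 0 to 0.10) and attrition (for example 0 to 20%).
- Correct the attrition sentence: 180 tolerates 18.9% loss, or state that 20% loss leaves 144 and 84.6% power before any clustering.

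No extra enrolment is asked for. The cost is a change of wording and of the order of analyses, about 2 points of power if the ICC is in fact zero, and a less favourable stated power.

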### Eligibility criteria

#### Inclusion criteria

1. Providing written informed consent.

2. Over the age of 18.

3. Clinical diagnosis of relapsing-remitting or progressive multiple sclerosis (Poser/McDonald criteria [48-50].

4. Score on the Fatigue Severity Scale (FSS) [51] greater than 4. The FSS is a uni-dimensional self-report measure consisting of 9 items that ask about severity of fatigue related to daily activities (such as physical functioning, exercise, work, family, and social life). Responses are made on a 7-point Likert-type scale.

5. Ambulatory (score on the Adapted Patient Determined Disease Steps (APDDS) Scale [52] < 8). This self-administered instrument is based on the Patient-Determined Disease Steps (PDDS) scale and the telephone Expanded Disability Status Scale (EDSS). The programme content will be most relevant for those who are ambulatory. Individuals who are non-ambulatory will continue to receive standard care.

6. Able to attend the intervention sessions.

7. English speaking.

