#### Recruitment and consent

Potential participants (identified via secondary or primary care or self-referred) will be sent a trial information pack (Key Facts sheet, a set of Participant Information Sheets, two screening measures (FSS & APDDS), response slips (interested to hear more/decline to participate, plus reasons why) and a prepaid envelope. They will be asked to return a reply slip and the two completed screening measures in a prepaid envelope to the Local Investigator (LI) if they wish to find out more about the trial, or a decline slip, if they would prefer not to receive any further information. Individuals who have not responded will be sent a second trial information pack two weeks later and a final invitation to participate one month later.

The LI in each centre will telephone those who have expressed an interest in the trial and give them an opportunity to ask questions. If, after this discussion, the individual still wishes to take part, the LI will undertake a screening using a checklist. After screening, participants will be notified via the telephone whether they are eligible or ineligible. Participants who are currently ineligible (e.g. due to medication recently started, a planned holiday, having received fatigue advice etc.) but who may fulfil eligibility criteria at a later date will be held over to be rescreened (if another iteration is scheduled in the centre). Individuals who are ineligible will be sent a letter notifying them of this, along with a booklet produced by the MS Society about MS-fatigue [54].

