#### Randomisation

To ensure good allocation concealment, random allocation will be e-mail-based and administered at Poole Hospital by the statistician who will be blinded to the identity of participants. Once a block of participants from a centre have provided informed consent they will be formally entered onto the trial database and an anonymised list of their identification numbers will be sent to the statistician who will randomly allocate half to the FMP group and half to the current local practice group. This method implies stratification by centre.

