### Outcome Measures

The following demographic information will be collected before the start of the trial: age, sex, educational attainment, marital status, number of children, length of time since diagnosis, disease course, relapse history, employment status, prescribed drugs currently taken, co-morbid medical conditions, disability level.

For those randomised to the FMP, outcomes will be measured 1 week prior to the start of the programme and 1 month, 4 months and 12 months after the end of the programme. For those randomised to current local practice, outcomes will be sent on the same dates as those randomised to the FMP.

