#### 1. Self-reported fatigue severity

The Fatigue Assessment Instrument (FAI) [55] is an expanded version of the uni-dimensional Fatigue Severity Scale (FSS) [51]. The FSS is one of the best known and most used fatigue scales. It principally measures the impact of fatigue on specific types of functioning. The FAI has four subscales: fatigue severity, situation specificity, consequences of fatigue, and responsiveness to rest/sleep. Responses are made on a 7-point Likert-type scale. The fatigue severity subscale of the FAI corresponds almost exactly to the Fatigue Severity Scale, sharing eight of the original nine items along with three additional items. Scores on this subscale are a primary outcome. The other subscales are secondary outcomes.

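### The screening FSS, the one fatigue score clearly taken before allocation, is named in no planned analysis, so no planned analysis guards against an allocation-influenced FAI baseline

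*Protocol article*

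**What the plan says.** **Screening.** Entry requires "Score on the Fatigue Severity Scale (FSS) [51] greater than 4" (Inclusion criteria). The information pack contains "two screening measures (FSS & APDDS"), and people who want to hear more are "asked to return a reply slip and the two completed screening measures" (Recruitment and consent). The telephone screening follows.

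**Allocation.** "Once a block of participants from a centre have provided informed consent they will be formally entered onto the trial database", after which the statistician allocates half of the block to each arm (Randomisation).

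**Overlap.** The FAI severity subscale, a primary outcome, is described as "sharing eight of the original nine items along with three additional items" (Primary Outcome Measures, item 1).

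**Baseline outcomes.** "For those randomised to the FMP, outcomes will be measured 1 week prior to the start of the programme", and "For those randomised to current local practice, outcomes will be sent on the same dates as those randomised to the FMP" (Outcome Measures).

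**Analysis.** The main comparison is an independent-samples t-test on change from baseline, excluding people with missing outcome data. Additional analysis 1 adjusts, among other things, as follows: "For each outcome variable analysed, these would include the baseline measurement for that outcome, baseline primary outcome measures, gender, age, marital status". Baseline FAI severity is therefore already a covariate. Additional analysis 3 uses last observation carried forward and a mixed model. Additional analysis 4 models all occasions together. Additional analysis 5 lists baseline fatigue as an effect modifier without naming the instrument. The FSS is named in none of these.

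**The concern.** The trial holds a near-parallel measure of its main outcome, complete for everyone and fixed before anyone knew their arm. The fatigue baseline that the analyses do use seems to be collected once arms are known. Participants report it themselves and cannot be blind, because one arm attends a group programme and there is no placebo.

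Two things are at stake. First, if knowing the allocation changes how people answer the baseline questionnaire, the shift enters the change score in full and the baseline-adjusted estimate in part, and no planned analysis would reveal it. Second, a participant who does not return the FAI baseline has no change score, even if all three follow-ups come back.

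**Working it through.** **1. Is the FSS complete and taken before allocation?** It is an entry criterion, so every eligible participant has one. It comes back with the reply slip, before the screening call. Allocation follows once a block has consented. Both properties follow from the text.

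**2. Is the FAI baseline taken after allocation?** The Outcome Measures section schedules the measurement one week before the programme for people described as already randomised, and on the same dates for controls. The economic Data Collection section also describes the control arm's equivalent time points as post-randomisation, a clause that can be read to include the pre-intervention one. No sentence states the order outright, and the flowchart is not shown. This step is an inference.

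**3. What would a shifted baseline do?** Let d be a between-arm shift in reported baseline FAI caused by knowing the allocation, in SD units, with all SDs equal to 1. The distortion of the treatment effect is slope × d in absolute size. Assumed values: d = 0.1; correlation of baseline FAI with follow-up r1 = 0.5; FSS with follow-up r2 = 0.5; FSS with baseline FAI r12 = 0.7.

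| Analysis | Slope on baseline FAI | Distortion | Share of 0.5 target |
|---|---|---|---|
| Change-score t-test | 1 | 0.10 SD | one fifth |
| Adjusted for baseline FAI | 0.5 | 0.05 SD | one tenth |
| Adjusted for baseline FAI and FSS | (0.5 − 0.5 × 0.7)/(1 − 0.49) = 0.29 | 0.03 SD | about 6% |
| Follow-up adjusted for FSS only | 0 | 0 | none |

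Only the last model is free of the shift. It must use follow-up FAI as the outcome, because a change score would bring the FAI baseline back in.

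**4. How much precision would FSS add to baseline FAI?** The proportional cut in residual variance is (r2 − r1·r12)² / [(1 − r1²)(1 − r12²)]. The documents give no correlations, so every input is an assumption.

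| r1 | r2 | r12 | Cut |
|---|---|---|---|
| 0.60 | 0.45 | 0.75 | (0.45 − 0.45)² = 0, so 0% |
| 0.50 | 0.50 | 0.70 | 0.0225/(0.75 × 0.51) = 5.9% |
| 0.60 | 0.60 | 0.80 | 0.0144/(0.64 × 0.36) = 6.2% |
| 0.70 | 0.70 | 0.70 | 0.0441/(0.51 × 0.51) = 17.0% |
| 0.45 | 0.60 | 0.60 | 0.1089/(0.7975 × 0.64) = 21% |

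The 21% case needs FSS to predict follow-up better than the FAI's own baseline does. For r12 of 0.8-0.9, r1 up to 0.6 and r2 equal to r1 or up to 0.1 lower, the range is 0% to 6.2%. With r1 from 0.4 to 0.7, r2 likewise and r12 from 0.7 to 0.9, power at 72 per arm rises by at most about 1.4 points.

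**5. Would the FSS-only model be too weak?** At 72 per arm, effect 0.5 SD and r1 = 0.5, power (normal approximation) is 0.851 for the change score and 0.934 adjusted for baseline FAI. Adjusted for FSS alone it is 0.905 if r2 = 0.4 and 0.934 if r2 = 0.5.

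**6. Does the sample size move?** For effect 0.5, two-sided 5% and 85% power, the two-sample t-test needs 72.8, so 73 per arm and 146 in total, as stated. 180 × 0.8 = 144, or 72 per arm, with power 0.846 (t) or 0.851 (normal approximation). None of this depends on the FSS.

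**The case against.** The strongest reply is that nothing here is an error. Additional analysis 1 already adjusts for baseline FAI severity, which carries eight FSS items. The closer the two measures are, the less FSS adds. The main analysis is unadjusted, so a further covariate would not touch it. On precision this stands. A reader might infer that omitting FSS wastes a material part of the trial's information, but the documents give no correlations to support that, and plausible values go down to zero. The cut-off at 4 also restricts the FSS range, which tends to lower its correlation with follow-up. People held over for a later iteration may have an older score, since the text does not say whether the FSS is repeated at rescreening.

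A reader might also infer that a definite number of participants will be lost. The documents give no rate of missing baselines. At an assumed 5% it would be 0.05 × 180 = 9, and a mixed model that treats baseline as one of the occasions could keep those with follow-up data. The text does not say whether it will. Carrying the last observation forward cannot help them, as it supplies no FAI baseline.

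Nor do the documents show that FSS is excluded from every analysis. Additional analysis 5 leaves its fatigue measure undefined, and choosing the range-restricted FSS there would be a preference, not a correction.

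Finally, the post-allocation timing is inferred. That is true and limits the weight of the point. But redundancy is no answer to a shifted or missing FAI baseline: the overlap is what makes FSS a usable substitute.

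**Conclusion.** The point holds in a narrow form. The screening FSS is complete, precedes allocation, overlaps in eight of nine items with the primary fatigue measure, and is named in no planned analysis. Neither the change-score t-test nor the FAI-adjusted model protects against a baseline influenced by allocation. An analysis with FSS as the only fatigue baseline would.

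The size is conditional. Under an assumed 0.1 SD shift, up to a fifth of the target effect is at risk in the main analysis. If the FAI baseline is in fact completed before participants learn their arm, this risk disappears and only the missing-baseline use and a small precision gain remain. That gain is 0% to about 17-21% of residual variance over the assumed correlations, and about 0-6% in the more plausible case. The FSS analysis also does nothing about allocation-influenced answers at follow-up. This is a modest, inexpensive improvement and does not show that the planned analyses are invalid.

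**What to change.** 1. Add to additional analysis 1 a sensitivity analysis of follow-up FAI severity, not change, with the screening FSS as the only fatigue baseline. For the same reason, leave out of this model the other baseline primary outcome measures, which are collected on the same occasion as the FAI baseline.
2. Include FSS as a covariate in the adjusted FAI severity models.
3. Where the FAI baseline is missing in those models, impute it from FSS and other pre-randomisation covariates, without using arm.
4. State whether baseline questionnaires are completed before or after participants learn their allocation, so that readers can judge how much the sensitivity analysis matters.

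The cost is wording and one additional model. The data are already collected, and neither the main analysis nor the sample size changes.

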3. It is likely that outcome data will be missing for some participants. In the main analysis such individuals will be excluded. However, the implied assumption that the data are "Missing Completely At Random" might not be correct, potentially leading to biased estimates of the effect of the intervention [75]. Two methods will be used to assess the extent to which this occurs: Firstly, we will use the "Last Observation Carried Forward" imputation method (which assumes no change in outcome when a data point is missing). Secondly, we will use a mixed model for repeated measurements.

4. Analysing the change in outcome from baseline to each time point will, we believe, result in the most clinically useful presentation of results. However, to gain a deeper understanding of how outcome measures change over the course of follow-up, we will also model all measurement occasions together for each outcome.

5. It is possible that the fatigue management programme might be more effective in certain sub-groups of individuals. We will examine these potential effect modifiers by testing the relevant "treatment x effect modifier" interaction terms. However, we acknowledge that these statistical tests are likely to be underpowered, since this was not a specific aim of the study. In these analyses, we will consider study centre, baseline fatigue, gender, age, marital status, type of MS, time since diagnosis, and level of disability.

These additional analyses will involve the use of a variety of techniques including multi-level/mixed models. In addition to these pre-specified analyses, we will also conduct further exploratory analyses as suggested by the data.

Presentation of the results will follow the Consolidated Standards of Reporting Trials (CONSORT) [76,77] guidelines, in such a way that they can be meaningfully incorporated into systematic reviews. The design of the trial will help ensure that it is graded as high quality in systematic reviews.

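### The main analysis is a complete-case t-test resting on a missing-data assumption the protocol itself doubts; the repeated-measures mixed model already planned should be primary, and LOCF is a poor check

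*Protocol article*

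**What the plan says.** Under Statistical analysis, the protocol article states: "The primary analysis will be an intention-to-treat analysis, whereby participants are analysed in the arm of the trial they were randomised to". The outcome analysed is the change from baseline, taken separately at each of three follow-ups (1, 4 and 12 months) and compared between arms with an independent-samples t-test. The reason given is that visit-wise change is the most clinically useful presentation.

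Additional analysis 3 in the same section says missing outcome data are likely, and of those participants: "In the main analysis such individuals will be excluded". It acknowledges that the MCAR assumption this implies may be incorrect and may bias the estimated effect. Two methods are named to assess how far this happens. The first is LOCF, glossed as a method "which assumes no change in outcome when a data point is missing". The second is a mixed model for repeated measurements. Additional analysis 4 also models all measurement occasions together.

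Under Sample size, power is said to hold "if 20% of participants do not provide data on the primary outcome measures".

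**The concern.** The analysis that carries the trial's conclusion uses, at each visit, only people with an outcome at that visit. At 12 months, someone who answered at 1 and 4 months and then stopped contributes nothing to the 12-month contrast, although the earlier answers say something about where that person was heading.

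The comparator is current local practice without a placebo, and all three primary outcomes are self-reported questionnaires. The reasons for not returning a questionnaire can therefore differ between arms. If they do, and if they relate to earlier scores, the complete-case difference in mean change is biased. A method that needs only the weaker MAR assumption is already in the plan but is not the one that decides the result. If the t-test and the mixed model disagree, the t-test stands as the main finding.

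LOCF, meant to show the extent of the bias, brings a bias of its own. A gap between LOCF and the main analysis therefore does not show that MCAR has failed.

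**Working it through.** **Inputs from the protocol article (Sample size; Outcome Measures).** Medium standardised effect, 0.5 ("In this trial, we will aim to detect a medium effect size"); 85% power; "using a two-tailed 5% significance level"; requirement stated as "is 73 people per arm of the trial; 146 in total"; 180 enrolled, 90 per arm; 20% missing allowed for; assessments at baseline and at 1, 4 and 12 months.

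**1. The plan's own figure.** The two-sample t-test solution for effect 0.5, 85% power and two-sided 5% is 72.8, so 73 per arm, as stated. The normal approximation gives 72. With 20% missing, 180 × 0.8 = 144, or 72 per arm, and power is 84.6% (t-test). The sample size is sound. The relevant figure is the loss: 180 × 0.2 = 36 people excluded from the main analysis if the allowance is used up.

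**2. LOCF under MCAR.**

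- At 1 month the last observation is the baseline, so a missing person is given zero change. With a fraction m missing, the LOCF effect is (1 − m) × true effect. For m = 0.20: 0.80 × 0.50 = 0.40. The complete-case estimate is unbiased here.
- At 12 months, suppose 20% are lost in three equal steps. The loss per step is 1 − 0.8^(1/3) = 0.072. Only those lost before 1 month are given zero change, if the true effect is constant over visits. LOCF then gives 0.50 × (1 − 0.072) = 0.464. A simulation with 400,000 per arm gave 0.46 to 0.47.

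**3. Complete-case bias at 12 months.** None of the following assumptions is in the documents. True effect −0.50 SD at every follow-up (lower is better); about 20% missing at 12 months in each arm; drop-out after 4 months by a logistic model with slope 0.8 per SD in the intervention arm and none in control, unless stated; 600,000 per arm. Correlation between visits is either 0.6 throughout (CS) or 0.75 per step, first-order autoregressive (AR).

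| Higher (worse) value of this makes drop-out likelier | Complete case, CS | Complete case, AR |
|---|---|---|
| 4-month change, intervention arm only | −0.56 | −0.61 |
| 4-month score, intervention arm only | −0.50 | −0.53 |
| 1-month score, intervention arm only | −0.50 | −0.47 |
| Baseline score, intervention arm only | −0.44 | −0.41 |
| 4-month change, same in both arms | −0.50 | −0.50 |

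An estimator that is valid under MAR, regressing the 12-month score on all earlier scores within arm, gave −0.50 in every row.

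**4. A different drop-out model.** Here loss occurs before each follow-up and depends on the last score, with slope 1 and correlation 0.6.

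| Mechanism | Complete case | LOCF | Mixed model |
|---|---|---|---|
| MCAR | −0.50 | −0.46 to −0.47 | −0.50 |
| Same in both arms | −0.50 | −0.46 to −0.47 | −0.50 |
| Worse scorers leave the intervention arm only | −0.47 to −0.48 | −0.39 to −0.40 | −0.50 |
| As above, and better scorers leave control | about −0.45 | −0.32 to −0.33 | −0.50 |

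**5. Scale.** With correlation 0.6 the SD of a change score is √(2 × 0.4) = 0.894. With 72 per arm the standard error of the difference is 0.894 × √(2/72) = 0.149 SD. The largest complete-case biases above, about 0.09 downward and 0.11 upward, are smaller than one standard error. Unlike sampling error, they do not shrink with sample size.

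**The case against.** The strongest reply is that the protocol is candid and already plans the better analysis. It defines intention-to-treat by allocated arm, undertakes to seek outcomes from everyone, discloses what LOCF assumes, and lists the mixed model as one of two checks. It does not rely on LOCF alone, and nothing says the mixed model ranks below LOCF. The 1- and 4-month data of later drop-outs are used in their own visit-wise comparisons. All of this stands. What remains is that the mixed model does not decide the result. The stated reason for the order, clinically useful presentation, does not require a t-test, because an arm-by-visit model also reports the difference at 1, 4 and 12 months.

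A reader might infer that the main analysis will overstate the benefit because participants who do not improve stop responding, and that LOCF errs the other way so that the two bracket the truth. The documents do not support this. They say nothing about the drop-out mechanism. The overstatement appears when drop-out follows change in the intervention arm; drop-out on baseline score gives an understatement, and under the score-based mechanisms in step 4 complete case and LOCF both understate. Nor is complete case valid only when missingness is unrelated to response: with the same mechanism in both arms, the arm difference showed no appreciable bias.

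The mixed model's recovery of 0.50 also follows from the way drop-out was generated, which was MCAR or MAR. If non-response depends on the unobserved 12-month score, the mixed model can be biased too, and people with no follow-up add almost nothing to it.

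**Conclusion.** The point holds as a matter of choosing the main analysis. The plan states a complete-case rule, expects appreciable missing data, doubts the assumption behind the rule, and already contains a method that needs a weaker one. That the mixed model is the better main analysis, and LOCF a poor diagnostic, can be said with confidence: 0.40 in place of 0.50 at 1 month with 20% missing is arithmetic.

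The size and sign of the complete-case bias cannot be said with confidence. The range of about 0.41 to 0.61 around a true 0.50 (18% too small to 22% too large) rests on assumed drop-out mechanisms, correlations and a constant effect, and includes no bias at all when the arms behave alike. The plan does not contradict itself here, and the sample size is unaffected. The change should be made, but the trial does not fail without it.

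**What to change.** 1. Make the planned mixed model for repeated measurements the primary analysis of each primary outcome: all follow-ups, arm-by-visit terms, baseline included, and the between-arm difference reported at 1, 4 and 12 months.
2. Keep the complete-case t-test on change scores as a sensitivity analysis.
3. Replace LOCF with delta-adjusted or control-based multiple imputation, to show how far the result depends on MAR.

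Clustering by intervention group is a separate item in the plan (additional analysis 2) and need not be settled here. No new data, visits or participants are needed. Items 1 and 2 mostly reorder analyses already listed, although baseline adjustment (now additional analysis 1) moves into the primary model. Item 3 is new work of modest size.
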